# Brain-computer interface on wrist training with or without neurofeedback in subacute stroke: a study protocol for a double-blinded, randomized control pilot trial

**DOI:** 10.3389/fneur.2024.1376782

**Published:** 2024-07-31

**Keywords:** stroke rehabilitation, brain machine interface, brain-computer interface, randomized clinical trial, clinical trial protocol

## Abstract

**Background:**

After a stroke, damage to the part of the brain that controls movement results in the loss of motor function. Brain-computer interface (BCI)-based stroke rehabilitation involves patients imagining movement without physically moving while the system measures the perceptual-motor rhythm in the motor cortex. Visual feedback through virtual reality and functional electrical stimulation is provided simultaneously. The superiority of real BCI over sham BCI in the subacute phase of stroke remains unclear. Therefore, we aim to compare the effects of real and sham BCI on motor function and brain activity among patients with subacute stroke with weak wrist extensor strength.

**Methods:**

This is a double-blinded randomized controlled trial. Patients with stroke will be categorized into real BCI and sham BCI groups. The BCI task involves wrist extension for 60 min/day, 5 times/week for 4 weeks. Twenty sessions will be conducted. The evaluation will be conducted four times, as follows: before the intervention, 2 weeks after the start of the intervention, immediately after the intervention, and 4 weeks after the intervention. The assessments include a clinical evaluation, electroencephalography, and electromyography using motor-evoked potentials.

**Discussion:**

Patients will be categorized into two groups, as follows: those who will be receiving neurofeedback and those who will not receive this feedback during the BCI rehabilitation training. We will examine the importance of motor imaging feedback, and the effect of patients’ continuous participation in the training rather than their being passive.

**Clinical Trial Registration:** KCT0008589.

## Introduction

1

Patients with stroke commonly face restrictions in their daily activities and social engagement because of impaired upper limb function, resulting in a decline in their overall quality of life (1). Rehabilitation enables the restoration of motor functions (2). Enhanced post-stroke function has been reported to result from recent approaches that incorporate more intensive and repetitive training, realistic and contextually relevant exercises, motivation, and active participation. These methods have been reported to be more effective than conventional and passive interventions (3, 4), and they use brain-computer interface (BCI) technology, demonstrating its efficacy in stroke rehabilitation regarding clinical functionality and neurophysiological changes (5, 6).

BCI acquires physiological signals, including brain waves, to accurately assess a patient’s intent and condition. Multimodal sensory stimulation has been adopted as a therapy involving mirror therapy, action observation, motor imagery (MI), and virtual reality (VR) training to acquire motor-relevant signals (7, 8). Meanwhile, feedback is needed to complete the motor performance loop and finally to accomplish plastic changes in the motor pathway, including creating alternative pathways or restoring the original pathway (9). Additionally, real-time feedback during the therapeutic process could augment this plastic change (10). Most importantly, the BCI was successfully operated by the closed loop connecting the motor intention to feedback, indicating the actual execution of motor tasks. This connection is necessary to effectively reorganize the specific neural circuits targeted in training, ultimately leading to functional improvement.

Earlier studies have shown the importance of the close relationship between motor intention and feedback (11–13). However, there is a lack of studies demonstrating the superiority of BCI operated using MI-contingent feedback (real BCI) over BCI operated using MI-irrelevant feedback (sham BCI). Two studies have only proven the superiority of real BCI over sham BCI. Ramos-Murguialday et al.’s study using BCI-driven finger orthosis (14) revealed a noteworthy enhancement in motor function, evident in the upper limb Fugl–Meyer assessment (FMA) scores of the real-BCI group compared to the sham-BCI group. In a separate study using FES as a feedback modality, Biasiucci et al. (15) also showed significant disparities in FMA improvement and wrist extensor muscle strength between real and sham BCI, favoring real BCI. However, these two studies enrolled only patients with chronic stroke. Thus, the favorable effects of real BCI were not confirmed in the subacute phase of stroke. Frolov et al. exhibited enhancements within a real-BCI group in patients with subacute and chronic stroke. However, they did not directly compare real-BCI and sham-BCI (16). Moreover, they did not enroll patients with subacute and chronic phase stroke separately at the beginning of the study. However, they analyzed them by categorizing them into subacute and chronic groups after the termination of the study.

A recent study demonstrated that functional recovery predominantly occurs within the first 2–3 months after stroke (17). Patients who undergo early rehabilitation therapy after a stroke tend to exhibit better outcomes, with significant recovery occurring within the early phase after stroke, such as the subacute phase (18, 19). Similarly, patients with subacute stroke benefit from training with a BCI. Wu et al. (20) demonstrated that the BCI significantly enhanced upper limb motor function and reorganized brain functional networks. Therefore, it needs to be verified whether real BCI is superior to sham BCI in the subacute phase of stroke. In this study, we aim to compare the effects of real and sham BCI on motor function and brain activity among patients with subacute stroke with weak wrist extensor strength.

The recently launched RecoveriX PRO system is a BCI-based rehabilitation training system for patients with stroke. The system measures the sensorimotor rhythm generated in the motor cortex during the imagined movement without external physical movement. Subsequently, it provides visual feedback through VR and induces movement through functional electrical stimulation (FES) (21). Importantly, feedback is provided only when the patient intends to move, encouraging active participation and enhancing neuroplasticity and the brain’s ability to self-restructure and reorganize in response to external stimuli. We will utilize RecoveriX PRO system for our proposed study to compare the effects of BCI on motor function and brain activity among patients with subacute stroke with weak wrist extensor strength.

## Methods and analysis

2

### Trial design

2.1

This intervention will be performed as a double-blind, parallel-group (1:1 ratio), randomized controlled trial. In addition, it will be conducted in an independent and quiet environment, where maximum concentration can be achieved with the BCI. The therapist will always be beside the participant in preparing for any issues during the intervention. We will assess the measures to determine the extent of improvement provided by the intervention over time. The CONSORT flow diagram is shown in Figure 1.

**Figure 1 fig1:**
[figure not shown]
CONSORT flow diagram.

### Participants

2.2

This study will be conducted at the National Rehabilitation Center in the Republic of Korea, and the experiment will be performed at the same center. The Institutional Review Board of the Rehabilitation Hospital approved this study (IRB no. NRC-2023-02-013). This study will involve human participants and aims to investigate the effects of BCI on subacute stroke. The study will be conducted in accordance with ethical statements and guidelines for human research. All participants who agree to participate after understanding the contents of this research will provide written informed consent before enrollment. This study was registered with CRIS (cris no. KCT0008589).

#### Inclusion criteria

2.2.1

The inclusion criteria are as follows: (1) hemiplegic participants secondary to a first-ever stroke with lesions confined to one hemisphere; (2) subacute stroke, which is defined as motor dysfunction occurring within 1 week to 6 months after stroke onset; (3) Medical Research Council (MRC) scale of affected wrist extensor muscle strength ≦ 2; (4) age > 19 years; and (5) a patient who has the cognitive ability to understand and follow the instructions of the researcher.

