### Sample size

2.5

We were unable to perform a sample size calculation owing to the absence of a prior study that compared real-BCI and sham BCI using the identical BCI system. Consequently, we have established a sample size of 20 for each arm, adhering to the minimum number suggested for pilot trials (32).

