### Assignment of interventions: allocation and blinding

2.7

Forty patients with stroke will be enrolled in this study. The random number table, which assigned the participants to either the real-BCI group or the sham-BCI group, was generated by PASS in the order of recruitment of participants. An external researcher will create a random number table and maintain it until the end of the study. The assignment will proceed by opening an opaque envelope containing a random number table in the order of participant recruitment. All participants will be blinded without knowledge of the group they will be assigned to.

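### The stated analysis makes no use of time since stroke and names no between-arm test, although eligibility runs from 1 week to 6 months; at 20 per arm this costs precision and interpretability, not validity

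*Protocol article*

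**What the plan says.** All references are to the protocol article.

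- **Eligibility (section 2.2.1).** The trial takes "subacute stroke, which is defined as motor dysfunction occurring within 1 week to 6 months after stroke onset".
- **Recovery (section 1, Introduction).** The authors cite evidence that "functional recovery predominantly occurs within the first 2–3 months after stroke". They also fault an earlier BCI study because "they did not enroll patients with subacute and chronic phase stroke separately at the beginning of the study".
- **Design and size (sections 2.1, 2.5, 2.7).** The trial is a "parallel-group (1:1 ratio), randomized controlled trial"; "we have established a sample size of 20 for each arm", so 40 in total. The size follows a rule for pilot trials, and the article says that no calculation was possible.
- **Allocation (section 2.7).** A random number table was generated in PASS, and an external researcher holds it. "The assignment will proceed by opening an opaque envelope containing a random number table in the order of participant recruitment". No stratification factor is named.
- **Analysis (section 2.11).** Repeated-measures ANOVA over T0, T2, T4 and T8, with paired t-tests as post-hoc tests. For non-normal data, the Friedman and Wilcoxon signed-rank tests are used within groups. No covariate and no group or group-by-time term is named.
- **Aim (sections 1 and 4).** To compare the effects of real and sham BCI.

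**The concern.** By the article's own account, where a patient sits between 1 week and 6 months after onset bears on how much recovery is still to come. The trial then measures change over 8 weeks. The variable is available for every patient because eligibility depends on it, yet the stated analysis does not use it.

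Two things are at stake. First, ignoring a prognostic variable leaves its variance in the error term, which matters when there are only 20 patients per arm. Second, if one arm happens to hold more recently affected patients, an unadjusted result is hard to interpret.

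A more basic gap lies beneath this. Tests over time will show natural recovery as improvement in both arms, even if the arms are perfectly balanced. Such tests do not answer whether real BCI does better than sham, and a covariate helps only once a between-arm comparison has been named.

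**Working it through.** **The plan's own figure.** The article gives no effect size, SD or power, so there is no calculation to reproduce. The sizes agree with each other: 2 × 20 = 40, as in sections 2.5 and 2.7.

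**Inputs.** From the article: 20 per arm, significance level 0.05 and the 1-week-to-6-month window. Assumed: a two-sided test; the share of outcome variance explained by time since onset (R² = 0.10, 0.25 or 0.40); a treatment effect of 0.8 SD; and, where stated, how enrolment times are distributed.

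**Step 1: how often the arms differ in time since onset.** In SD units, the difference in means has standard error √(2/20) = 0.316. A gap of at least 0.5 SD corresponds to z = 0.5/0.316 = 1.58, so P = 0.114.

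In days, if enrolment were uniform over 7 to 180 days (assumption):

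- SD = (180 − 7)/√12 = 49.9 days, so 0.5 SD is about 25 days.
- Standard error of the difference = 49.9 × 0.316 = 15.8 days.
- P(gap > 21 days) = 0.18; P(gap > 30 days) = 0.06.

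As an early/late split (hypergeometric, 40 patients, 20 per arm), the share of early patients differs by at least 20 percentage points with probability 0.30 if 30% or 70% are early, and 0.34 if 50% are early.

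**Step 2: what such a gap does to the outcome.** A gap of 0.5 SD shifts the outcome difference by 0.5 × √R². That is 0.16 SD at R² = 0.10 and 0.25 SD at R² = 0.25. The standard error of the unadjusted outcome difference is itself 0.316 SD.

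**Step 3: error rate and power.** Simulation of a between-arm comparison, 20 v 20, 40,000 runs per setting, comparing an unadjusted t-test (38 df) with ANCOVA on time since onset (37 df):

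| | R² 0.10 | R² 0.25 | R² 0.40 |
|---|---|---|---|
| Type I error, all trials, unadjusted | 0.051 | 0.050 | 0.051 |
| Type I error, all trials, adjusted | 0.050 | 0.051 | 0.048 |
| Type I error, gap ≥ 0.5 SD, unadjusted | 0.084 | 0.130 | 0.187 |
| Type I error, gap ≥ 0.5 SD, adjusted | 0.047 | 0.055 | 0.046 |
| Power at 0.8 SD, unadjusted | 0.691 | 0.691 | 0.696 |
| Power at 0.8 SD, adjusted | 0.726 | 0.804 | 0.884 |

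The rows for a gap of at least 0.5 SD rest on about 11% of the runs.

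**Step 4: the gain in patients.** Adjustment is worth roughly 1/(1 − R²): 1/0.90 = 1.11 and 1/0.75 = 1.33. Twenty per arm would then work like 20 × 1.11 ≈ 22 or 20 × 1.33 ≈ 27.

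**Limits.** The simulation uses a continuous outcome, whereas the primary outcome is the 0–5 MRC grade in patients who start at 2 or below. If the baseline score is also in the model, the relevant R² is what time since onset adds beyond it, which may be smaller.

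**The case against.** The strongest reply is that randomisation already allows for chance imbalance. This stands: the unadjusted error rate is about 5% over all trials in every column. A reader might infer that imbalance in spontaneous recovery makes the design biased, or makes a false BCI effect likely. The figures do not support that. The raised rates of 8% to 19% apply only to the roughly 11% of trials that turn out unbalanced.

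The second reply is that this is a condensed article on a pilot trial, and covariates may be set in an analysis plan that is not shown. This stands in part. The absence of a covariate alone would be weak ground. But section 2.11 does state its tests, and those tests address change over time and not the comparison that is the aim.

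Other tempting readings also go too far:

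- *Allocation is unstratified.* Section 2.7 names no stratum, but it does not say whether the PASS list is simple, blocked or stratified.
- *Concealment is lost.* The envelope sentence can be read as one envelope holding the whole table. It is equally compatible with one opening per participant, since an external researcher keeps the table.
- *The authors repeat the fault they criticise.* Their criticism concerns mixing subacute with chronic patients, and this trial's window ends at 6 months.
- *Time since onset is the strongest predictor.* The Introduction says when recovery mostly happens; it does not rank predictors.

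**Conclusion.** The point holds as one of precision and interpretability. The window is wide relative to the recovery period that the article itself describes, the variable is known for every patient, and the stated analysis neither uses it nor names the between-arm comparison in which it would be used.

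The probability of an imbalance of at least 0.5 SD, about 11%, follows from the arm sizes with a normal approximation. The gain in power from about 0.69 to 0.73–0.80 rests on an assumed R² of 0.10 to 0.25 and an assumed effect of 0.8 SD, and is indicative only for the ordinal MRC grade. No bias in the design and no failure of concealment is shown.

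**What to change.** **Main change, section 2.11.** Name the comparison of real with sham BCI and pre-specify the baseline score and days since stroke onset as covariates. Either form would do:

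- a baseline-adjusted comparison at T4; or
- a group-by-time model with T2, T4 and T8 as responses and the T0 score as a covariate. Days since onset should then also interact with time, because a main effect alone does not adjust the group-by-time contrast.

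If the MRC grade is analysed as ordinal, carry the same covariates into that model. At a single time point this costs one or two degrees of freedom (from 38 to 37 or 36) and needs no new data. The choice should be recorded before any outcome is compared by arm.

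**Secondary, section 2.7.** If the procedure is one assignment per sequentially numbered, sealed, opaque envelope, say so. This is a change of wording only.

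**Optional.** Stratify the assignments not yet made by time since onset. The list has already been generated for an approved and registered trial, and part of it may have been used, so this is not clearly cheap and would improve balance only in the remainder. The covariate gives most of the benefit without it.

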#### Exclusion criteria

2.2.2

The exclusion criteria are as follows: (1) factors impeding recording of electroencephalogram (EEG) signals such as skin infections, scalp wounds, and the presence of metal implants under electrodes; (2) spasticity of wrist flexor, scoring ≥2 on the modified Ashworth scale; (3) cognitive impairments or severe aphasia hindering the ability of the participant to understand and follow the instructions during the research; (4) presence of a neurological or psychiatric disorder other than stroke; (5) musculoskeletal problem or severe pain of the affected upper limb impeding intervention; (6) hemispatial neglect; (7) patients with epilepsy.

### Interventions

2.3

#### BCI-FES system

2.3.1

The BCI intervention tool employed in this study is the RecoveriX PRO, a noninvasive neurofeedback-based stroke rehabilitation system developed by g.tec Medical Engineering GmbH in Austria. The system integrates an EEG, FES, and a computer screen projecting virtual hands. The EEG signals are recorded using a g. nautilus PRO FLEXIBLE (g.tec Medical Engineering GmbH, Austria). There are 16-channel systems (FC3, FCz, FC4, C5, C3, C1, Cz, C2, C4, C6, CP3, CP1, CPz, CP2, CP4, and Pz) that capture data from specific locations according to the internationally recognized 10–20 systems. The g. Nautilus PRO FLEXIBLE allows plug-in electrode strands with Strand 16 g SCARABEO (g.tec Medical Engineering GmbH, Austria) gel-based EEG electrodes. The ground and reference electrodes are positioned on the forehead (FPz) and right earlobe. Spatial filtering, which employs the common spatial pattern method, aims to maximize the variance for one category of MI and minimize the variance for the other, followed by linear discriminant analysis for classification. FES electrodes are placed over the wrist extensors of both forearms, with a frequency of 50 Hz and a rectangular pulse width of 300 μs using g.Estim FES devices (g.tec medical engineering GmbH, Austria). The current amplitude will be customized to ensure contraction of the wrist extensor muscles on the affected side without pain, spasms, or fatigue. In the virtual avatar format, both hands and arms are placed on a table with a cheese-shaped cube positioned between them on the screen (Figure 2). Visual feedback is provided through a game where the objective is to compete with a mouse to protect a food item (cheese). At the start of each session, 80 pieces of cheese are placed between the two virtual arms. During each exercise, the mouse emerges from either the right or left corner of the room (corresponding to the wrist that must be moved) and is situated near the pile of cheese pieces. The RecoveriX PRO system integrates, analyzes, and recognizes EEG signals associated with MI, activating the FES system when the participants imagine movements on the instructed side. The RecoveriX PRO implements paired associative stimulation, connecting recorded MI with output feedback through visual feedback (virtual avatar wrist extension) and FES for wrist extension. Consequently, the system establishes a closed loop between brain signals during the desired MI and contingent visual and proprioceptive feedback, aiding patients in learning to imagine or perform the desired movements. The study setting is illustrated in Figure 3.

**Figure 2 fig2:**
[figure not shown]
Virtual avatar of RecoveriX PRO intervention.

**Figure 3 fig3:**
[figure not shown]
RecoveriX PRO study setting.

#### Intervention description

2.3.2

The RecoveriX PRO interventions involve 240 trials of MI tasks for both hands, which are further classified into three runs of 80 trials each. Each run consists of two sets of 40 trials, with a 2-min break between consecutive sets and a 3-5-min break between runs. A trial is initiated with an attention beep at 0 s. The corresponding verbal instructions (“left” or “right”) in the participants’ native language will be presented at 2 s. The MI task involves imagining wrist dorsiflexion based on the system’s instruction, which indicates “left” or “right” in a random order. During the feedback phase (from 3.5 s to 8 s), the FES and virtual avatar are activated. The interventions comprise two types of runs: calibration and training. The primary distinction is the feedback phase (MI-contingent feedback vs. MI-independent feedback). In the calibration run, feedback is consistently activated regardless of the MI. Contrarily, in the training run, feedback is only activated when the BCI system detects the MI of the correct hand. The feedback is updated five times per second. More importantly, the calibration run is combined with FES in each session. The relaxation signal is presented at 8 s, and the task period (MI) lasts 6 s. RecoveriX PRO rehabilitation procedure is presented in Figure 4.

**Figure 4 fig4:**
[figure not shown]
RecoveriX PRO rehabilitation procedure.

All participants will undergo 20 sessions of 60-min BCI intervention (real BCI intervention or sham BCI), 5 days a week for 4 weeks, administered by research physical therapists. The real BCI intervention session includes one calibration run and two subsequent training runs in which participants will receive an MI-contingent feedback-based BCI intervention. In contrast, the sham BCI intervention session comprises three consecutive calibration runs without any training runs. Thus, participants will receive MI-independent feedback (FES and visual feedback) on either hand, regardless of their MI. The participants will perform the MI task seated while wearing an EEG cap and observing the virtual avatar’s forearm and hand on a screen. The intervention and assessments will be conducted in an independent and quiet research room within a rehabilitation hospital, enabling a focused approach toward the task during the intervention.

Additionally, all participants will receive 30 min of conventional therapy for the affected upper limb 5 days a week for 4 weeks. The progress or response to therapy will be assessed after each session, and the results will be subsequently calculated. The accuracy plot is a metric for distinguishing left and right movements, indicating how well the participant performed MI during exercise. If the accuracy plot fails to surpass a significant threshold, an additional calibration exercise will be conducted to facilitate the smooth progression of the training mode.

